### TeamCare-PCN intervention

#### Overview

The TeamCare-PCN intervention involves a registered nurse Care Manager (CM), who coordinates collaborative team management for patients with diabetes and depression. Individuals with diabetes will be screened for depressive symptoms using the PHQ-9; patients with a score of > = 10 on the PHQ-9 are eligible for the intervention [43,44]. The PHQ-9 has been used in a number of interventions for screening of depressive symptoms in primary care [44], including among diabetic patients [45], and specifically in the efficacy study of the TEAM Care intervention [29].

The goal of the intervention is to reduce depressive symptoms, achieve targets for cardio-metabolic measures and improve lifestyle behaviors. The intervention includes three phases: (1) managing depression and improving depressive symptoms, (2) managing diabetes and controlling blood glucose, blood pressure and cholesterol, and (3) improving lifestyle behaviors such as healthy eating, physical activity and smoking cessation. The CM will coordinate the TeamCare-PCN intervention, while the family physician will remain responsible for final treatment decisions and all prescriptions. The CM will consult with specialists (psychiatrist and internist/endocrinologist) to consider management options depending on patients’ needs and desires. The CM will use locally endorsed evidence-based algorithms to provide recommendations for changes in the treatment plan, and in collaboration with specialists and the patients’ family physician, also support the implementation of the patients’ individualized care plan. Using a patient-centered focus, the CM will partner with the patient to develop a shared definition of problems, provide education and support, agree on specific targets/goals and individualized action plan, offer support and problem solving to optimize self-management, and closely monitor treatment adherence and outcomes.

#### Patient management

Patients entering the intervention will have a two-hour baseline appointment with the CM. This first visit will include a bio-psychosocial semi-structured assessment (reviewing medical history, previous treatments for depression and diabetes), patient education, potential treatment options (anti-depressant medications and/or psychotherapy) and developing an overall individualized care plan.

As mentioned, the intervention will consist of 3 phases; the first focusing on depression management, the second on cardio-metabolic diabetes management, and the third on general lifestyle modifications. A treat-to-target/stepped care approach will be used at each phase of the intervention. Recommended treatments have been based on algorithms that were developed in collaboration with the PCNs by compiling various guidelines and sources, such as extant clinical practice guidelines and consulting experts in the field. The CM will actively follow-up by telephone or in person one to two times per month to re-assess symptoms, and assist and support patients in achieving treatment goals. The CM will also have weekly meetings with the consulting specialists to review new cases and patient progress, and then communicate team treatment recommendations to the primary care physician.

The depression management phase (Phase 1) will involve the use of anti-depressant medications and/or referral for psychotherapy, as determined by the CM and the family physician (with study psychiatrist consultation as needed by the CM), tailored to each patient. A two-day training session for CM and consultant specialists was planned at the beginning of the project, with an annual one-day booster session The CM will be given basic training in three psychotherapeutic techniques during this phase: problem-solving therapy [46-49], behavioral activation [50-54], and motivational interviewing [55-57]. Direct referral to the care of a psychiatrist will occur only on failure of two separate trials of anti-depressants, or one trial of anti-depressant in combination with psychotherapy. Once patients have reached remission, the CM and patient work together towards a relapse prevention plan to help the patient identify when and where to seek help with future depressive symptoms or renewed problems for disease control. The CM will continue to work with patient through Phases 2 and 3 of the intervention.

Stepped care/treat-to-target algorithms for Phase 2 (cardio-metabolic care) were developed in collaboration with health care professionals at the PCNs and study specialists using local and national guidelines. Phase 2 includes working with the CM in analogous fashion to Phase 1, but with a focus on reaching individualized targets for hemoglobin A1c, lipids and blood pressure measures. Phase 3 involves patient education to address lifestyle behaviors such as diet and exercise. Locally developed educational materials and existing PCN support programs will be available for patient referrals.

### Usual care

All participants in TeamCare-PCN will be actively screened for depression and those allocated to usual care (or intervention) will be identified as such to their family physician. For disease management, patients will receive care from their family physician, without additional active support from the CM. Therefore, this group will receive the usual standard care for diabetes and depression from their family physicians based on available clinical practice guidelines. Participants in this group will be assessed for all of the same outcome measurements as intervention patients. A recently published trial concluded that screening for depression with written feedback to patients and physicians resulted in no improvements in depressive symptoms, nor changes in utilization of mental health care services [58]. Thus, in our design, the usual care group is very likely to represent usual care for patients with diabetes and depression.

### Outcome measures

To assess the effectiveness (“E” in RE-AIM) of TeamCare-PCN, we will use two primary outcome measures. First, given that we selected patients on the basis of depressive symptoms, our primary depression-related outcome will be the PHQ-9 scores at 12 months. Second, a global measure of patient-centered improvement (the scaled marginal model, see Analysis below) based on the combination of chronic disease-related clinical outcomes. All outcomes will be measured in all participants (i.e., both groups) at baseline, 6, and 12 months. We will secondarily evaluate process indicators for care received, as well as a host of patient-reported outcome measures to determine the overall effectiveness of the TeamCare-PCN intervention.

#### Depression-related outcome

The outcome measure for depression will be improvement in PHQ-9 score [43,44]. The minimal important difference on the PHQ-9 score is widely considered to be 5 points [44]. A remission of depression symptoms is indicated with a score <10 for a period of three consecutive months [29]. Operationally, this can be conceptualized as a continuous score or as a binary outcome: improved vs not, since all participants will have scores greater than 10 as part of their eligibility.

#### Chronic disease-related clinical outcomes

Clinical outcome measures include systolic blood pressure (SBP), LDL cholesterol and A1c, demonstrated by achievement of targets or significant improvements as indicated with a 10% improvement over baseline [59,60]. These outcomes will be measured using point-of-care devices that we have standardized and placed in each PCN. Capillary blood samples will be collected from participants to assess A1c and lipid profile. Cardiovascular (blood pressure and resting heart rate) and anthropometric (weight, height, and waist circumference) measurements will also be assessed at clinic visits. Regular, monthly quality assurance checks will be conducted on the point-of-care devices, validated against central laboratory measurements.

#### Process of care indicators

Process indicators will include the number of visits with PCN care providers, including CM, family physicians, specialists consults, referrals for mental health care, and use of medications and psychotherapeutic sessions. The time spent with patients will be tracked for all CM contacts. Adjustments to medications and adherence to treatments will also be assessed.

#### Patient-reported outcomes

A range of patient-reported outcomes will be collected from all participants by regularly administering previously validated surveys at baseline, 6 and 12 months. Survey sections and measures are outlined below, and a briefer version of the survey will be used at 6-months. These measures of patient-reported outcomes were selected based on extensive literature supporting their psychometric properties and common application in assessments of this patient population

 · *Health Related Quality of Life:* includes assessment of general health status (SF-12 and EQ-5D) [61-64] and diabetes-specific stress (Problem Areas in Diabetes 5-item) [65].

 · *Health behaviors and self-management:* includes assessment of smoking behaviors, alcohol consumption [66], substance use [67], and physical activity [68], and the Summary of Diabetes Self Care Activities (SDSCA) [69].

 · *Satisfaction with care*: using Consumer Assessment of Healthcare Providers and Systems (CAHPS), Adult Primary Care 1.0 [70] and Patient Assessment of Chronic Illness Care (PACIC) [71,72].

 · *Health Literacy and Self-efficacy:* includes assessment of health literacy (3-brief screening questions [73] and self efficacy (Stanford Self-Efficacy for Managing Chronic Disease 6-Item Scale) [74].

### Data management

The depression and medical outcome measures will be entered into a clinical management tracking system as part of the TeamCare-PCN intervention. The data collected in the survey and through clinical measurement will be entered into centralized, web-accessible databases. These study databases will be housed on secure servers in the research offices at the University of Alberta. Double data entry will be conducted and research staff will remain masked to allocation status at all times. Once the study is completed, all data will be exported and merged, based on individually assigned study ID numbers, to form an analyzable dataset. Investigators, research assistants, and analysts will be masked to allocation status at all times.

### Data analysis

As the initial focus of the intervention is on the management of depressive symptoms, we have considered the PHQ-9 as a main primary outcome, and will assess changes in PHQ-9 scores over 12-months between groups, adjusting for baseline PHQ-9 score, using a mixed effects multivariate model. For our second primary outcome of improvements in global disease control, we will employ a multivariate model that jointly tests the changes in multiple clinical outcomes, namely A1c, LDL cholesterol and systolic blood pressure [29]. Using the same analytic approach as in the recently published RCT of this intervention, we will apply a scaled marginal model [29,75] to simultaneously compare the change in these continuous outcomes at 12 months, adjusting for the baseline status for each variable. This approach scales the changes in each outcome by its standard errors, and thus the coefficients can be directly interpreted as effect sizes [29]. In either primary outcome analyses, the models will be estimated iteratively and the potential correlations among and between outcomes within individuals will be handled using generalized-estimating equation (GEE) models for each outcome [75].

We will also compare the study arms based on the proportion of subjects who achieved a remission of depression (i.e., PHQ-9 < 10 for 3 consecutive months) and the proportion of patients who achieve a clinically important change in the outcomes (that is, achieving a reduction of 5 points on the PHQ-9 [44] or a 10% or greater improvement over baseline values for A1C, LDL cholesterol and SBP at 12 months) [59,60], using generalized estimating equations and multivariable logistic regression models. This approach will allow us to present and interpret all outcomes in terms of absolute differences and a number-needed-to-treat [76].

For all analyses we will employ an intention-to-treat framework for our primary analysis, using a last-observation-carried-forward method of imputation for subjects who do not have complete follow-up data for primary or secondary outcomes. This approach is conservative as it assumes subjects with missing follow-up data have not changed. In either case, the regression models will accommodate additional covariates, as required, to adjust for PCN site, as well as any post-allocation baseline differences between groups in clinically important (e.g., age, sex) or statistically significant (e.g., p < 0.1) characteristics. This ability to statistically control for potential imbalance may be necessary given the non-random treatment allocation used in our “on-off” design.

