**Methods/design:**

We initiated the TeamCare model in four Primary Care Networks in Northern Alberta. The intervention involves a nurse care manager guiding patient-centered care with family physicians and consultant physician specialists to monitor progress and develop tailored care plans. Patients eligible for the intervention will be identified using the Patient Health Questionnaire-9 as a screen for depressive symptoms. Care managers will then guide patients through three phases: 1) improving depressive symptoms, 2) improving blood glucose, blood pressure and cholesterol, and 3) improving lifestyle behaviors. We will employ the RE-AIM framework for a comprehensive and mixed-methods approach to our evaluation. Effectiveness will be assessed using a controlled “on-off” trial design, whereby eligible patients would be alternately enrolled in the TeamCare intervention or usual care on a monthly basis. All patients will be assessed at baseline, 6 and 12 months. Our primary analyses will be based on changes in two outcomes: depressive symptoms, and a multivariable, scaled marginal model for the combined outcome of global disease control (i.e., A1c, systolic blood pressure, LDL cholesterol). Our planned enrolment of 168 patients will provide greater than 80% power to observe clinically important improvements in all measured outcomes. Direct costing of all intervention components and measurement of all health care utilization using linked administrative databases will be used to determine the cost-effectiveness of the intervention relative to usual care.

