### Recruitment and allocation

Recruiting participants into TeamCare-PCN involves three steps. * First *, a screening survey accompanied with an endorsement letter from the PCNs will be mailed out to all patients with type 2 diabetes on the PCNs’ diabetes registries. This survey asks about age, the ability to read and speak English, having type 2 diabetes, length of time since diagnosis, and screens for depressive symptoms. * Second *, after potential participants have completed and returned the screening survey, PCN staff will contact eligible participants to confirm all eligibility criteria and if the participant is willing to participate, and schedule a baseline assessment visit. * Third *, during the baseline visit, the Care Manager (CM) will confirm eligibility, explain the intervention, provide an intervention-specific information letter and obtain a signed written informed consent from the patient to participate in the study.

Participants will be allocated to study groups using a previously successful “on-off” group assignment method (Figure 1) [39,41,42]. Eligible and consenting respondents who book for a baseline assessment with the CM during month 1 will be allocated to the intervention arm (ON-group). Those who book the baseline assessment in month 2 will be allocated to the usual care arm (OFF-group). This allocation process will continue until the target sample size is recruited. This method has been used in many quality improvement studies, reliably leads to balance in measured [and unmeasured] patient characteristics [39,41,42], and meets study design criteria for internal validity sufficient to permit inclusion in the Cochrane Collaborations’ Effective Practice and Organization of Care (EPOC) systematic reviews [40]. Because all four sites are involved in both “on” and “off” phases, this particular study design also balances case mix and controls for Hawthorne or volunteer effects, as well as issues related to “institutional learning” over time [39,40,42].

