### Sample size and power considerations

We estimate that a minimum total sample size of 120, with 60 in each arm, would provide power of 0.80 to detect a mean difference of 5 points in the PHQ-9 [44], assuming a repeated measures correlation of 0.6, and 2-tailed alpha of 0.05. This sample size also provides more than 80% power (two sided alpha = 0.05) to detect any between-group absolute difference in proportions of 15% or more (e.g., 45% of usual care patients achieve depression remission vs 60% of intervention patients) [29]. Anticipating a 40% attrition rate, we planned to recruit 168 patients in total across our 4 PCN sites. Although the model is implemented in 4 PCN sites, the individual general physicians affiliated with the PCN will carry out the changes in care. While we will include PCN site as a covariate in our analysis, because there are approximately 140 general physicians across these 4 PCN sites, we choose not to further inflate our sample to account for clustering of patients and their outcomes.

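### Arm is set by whole booking month, but the stated primary analyses and power calculation make no allowance for month, so the 5% level and 0.80 power are not assured if outcomes correlate within month

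*Protocol article*

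**What the plan says.** **Allocation.** The abstract says patients are "alternately enrolled in the TeamCare intervention or usual care on a monthly basis". Recruitment and allocation gives the rule: "Eligible and consenting respondents who book for a baseline assessment with the CM during month 1 will be allocated to the intervention arm (ON-group", then "Those who book the baseline assessment in month 2 will be allocated to the usual care arm (OFF-group", and "This allocation process will continue until the target sample size is recruited". The number of months is not given. All four PCNs run both phases.

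**Analysis.** Data analysis specifies a baseline-adjusted mixed effects model for PHQ-9 and a scaled marginal model for A1c, LDL cholesterol and systolic blood pressure. For either primary outcome, "potential correlations among and between outcomes within individuals will be handled using generalized-estimating equation (GEE) models for each outcome". The same section allows covariates for PCN site and for baseline imbalance, and says these may be needed "given the non-random treatment allocation used in our" on-off design. It mentions no month, period or allocation-block term.

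**Sample size.** The calculation uses 60 patients per arm, power 0.80 for 5 PHQ-9 points and "2-tailed alpha of 0.05". On clustering, it mentions the four sites and about 140 physicians and concludes "we choose not to further inflate our sample to account for clustering of patients and their outcomes".

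**The concern.** Arm never varies within a booking month, so the treatment contrast compares a limited set of ON months with a limited set of OFF months. Anything that patients booked in the same month share (mailing wave, season, visit dates, point-of-care device status, staffing) goes wholly into one arm. If such influences shift outcomes after baseline adjustment, patients in a month are not independent replicates of the arm effect. An analysis that treats them so gives standard errors that are too small.

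The clustering that the plan does discuss is of another kind. Each site contributes patients to both arms, and nothing ties a physician's patients to one arm. Booking month is the grouping nested within arm, and it is the one left out. Covariate adjustment deals with imbalance in measured characteristics. It does not change the variance or degrees of freedom of a contrast allocated by month.

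At stake are the p-values and confidence intervals of both primary outcomes, and the stated power.

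**Working it through.** **Inputs from the article.** Recruited 168; evaluable 120 (60 per arm); two-sided alpha 0.05; power 0.80 for 5 PHQ-9 points; repeated-measures correlation 0.6; monthly alternation; four PCNs.

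**Assumed, because not given.** Recruitment over M = 12, 18 or 24 months; month ICC 0.01 to 0.10, with 0.05 as the reference; one ON/OFF calendar common to the four PCNs, which is how the allocation text reads.

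**1. The plan's own figure.** The 0.80 at 60 per arm cannot be reproduced, because no SD is stated. Solving 60 = 2(1.96 + 0.84)² SD² / 5² gives SD ≈ 9.8. Using the 0.6 correlation through a change score, with variance factor 2(1 − 0.6) = 0.8, gives 9.8/√0.8 ≈ 10.9. With an assumed SD of 5 to 7 and no correlation used, 60 per arm has at least 97% power. Below, 0.80 is taken at face value.

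**2. False-positive rate, month effects shared by all PCNs and independent between months.** Patients per month m = 168/M; design effect DE = 1 + (m − 1) × ICC; true alpha = 2[1 − Φ(1.96/√DE)].

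| M | m | DE at ICC 0.05 | alpha at 0.05 | alpha at 0.01 | alpha at 0.10 |
|---|---|---|---|---|---|
| 12 | 14 | 1.65 | 12.7% | 6.5% | 19.6% |
| 18 | 9.3 | 1.42 | 10.0% | 6.0% | 14.8% |
| 24 | 7 | 1.30 | 8.6% | 5.7% | 12.1% |

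At ICC 0, DE = 1 and alpha is 5%. Simulations of a patient-level test at ICC 0.05 gave about 13% to 14%, 10% to 11% and 9% to 10% for the three values of M. They run slightly above the formula because monthly numbers vary.

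**3. Month effects specific to each PCN.** Cells hold 168/(12 × 4) = 3.5 or 168/(24 × 4) = 1.75 patients. At ICC 0.05, DE is 1 + 2.5 × 0.05 = 1.125 or 1 + 0.75 × 0.05 = 1.038, so alpha is 6.5% or 5.4%. Simulation gave about 6% to 7%.

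**4. Shared month effects that persist from month to month.** Simulated at ICC 0.05 for 12, 18 and 24 months:
- autocorrelation 0.5: 8.0%, 7.2%, 6.0%
- autocorrelation 0.8: 6.1%, 5.9%, 5.6%
- pure annual cycle: 5.1%, 5.3%, 5.3%

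**5. Month-level test as the remedy.** A t-test on month means ran at about 5% under independent month effects. It fell to about 2% to 4% under autocorrelation of 0.5 to 0.8, and lower still in some seasonal settings.

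**6. Power with 120 evaluable patients, ICC 0.05, shared independent effects.** Power = Φ(2.80/√DE − 1.96), with m = 120/M.

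| M | m | DE | power |
|---|---|---|---|
| 12 | 10 | 1.45 | 0.64 |
| 18 | 6.7 | 1.28 | 0.70 |
| 24 | 5 | 1.20 | 0.72 |

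This uses a normal critical value. A t critical value based on months (2.228 for 12 months, 10 df) would lower power further.

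**The case against.** The strongest reply is that the problem is conditional and may be small.

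- **No correlation is documented.** At ICC 0 the test is exact. At ICC 0.01 with 18 to 24 months the excess is about one percentage point or less. This stands.
- **The largest figures need month effects that hit all four PCNs at once and last one month.** Several plausible sources are local: devices sit in each PCN and bookings go through PCN staff. Others, such as season, change slowly, and monthly alternation then places ON and OFF months under nearly the same conditions. Both points stand, and steps 3 and 4 show how much they reduce the excess.
- **A month-based analysis is not free.** It becomes conservative when month effects are smooth. This stands and belongs with the fix.
- **The random effects of the PHQ-9 model are not listed, and an unseen analysis plan might include month.** This stands in part. A reader might infer that the PHQ-9 model certainly treats patients booked in the same month as independent, but the text does not say so. The article is not merely silent, however: it names the dependence handled in both primary analyses and argues its position on clustering, and month appears in neither place.
- **The power loss starts from a figure that cannot be reproduced.** This stands. If the true SD is well below 10, the loss for a 5-point difference could be slight.

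None of this removes the mismatch between the unit of allocation and the stated analysis.

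**Conclusion.** The point holds in conditional form. Arm is allocated by booking month, and the stated models and power calculation make no allowance for it, so the 5% level and the 0.80 power are not assured. A reader might go further and conclude that the standard errors are too small and the error rate is broken. The article does not support that, because it gives no within-month correlation.

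Under the assumed ICC of 0.05 with 168 patients, the true false-positive rate is about 9% to 14% for 24 down to 12 months if month effects are shared and independent. It is about 6% to 8% if they are PCN-specific or autocorrelated, near 5% for a pure seasonal cycle, and 5% at ICC zero. Power stated as 0.80 would be about 64% to 72% under shared independent effects, if the 0.80 is accepted. The change is worth making because the upper part of this range would matter for both primary conclusions and the remedy is cheap.

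**What to change.** **Data analysis.** Include booking month as a random intercept in the PHQ-9 model, with small-sample degrees of freedom based on the number of months. For the scaled marginal model, cluster the GEE on booking month rather than on the individual, with a small-sample-corrected variance. Use a month-level summary test as a check. A PCN-by-month term is optional, because cells would hold only about 2 to 4 patients and its variance would be poorly estimated.

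**Sample size and power considerations.** State the expected number of allocation months, say that the 0.80 assumes no correlation within booking month, and show power over a range of ICCs. State the SD as well, so that the starting figure can be checked.

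**Cost.** Some wording and a few lines of code. Booking month must already be known because it determines the arm, so no extra patients or data are needed. The downsides are wider intervals, some loss of power, and a conservative test if month effects are smooth or seasonal, since alternation already cancels part of that variation.

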## Methods

### Overall study design

We will evaluate the effectiveness (i.e., the “E” in RE-AIM) of the TeamCare-PCN intervention using a controlled pragmatic trial design. We have implemented a variant of a practical design referred to as “cohort multiple RCT” (Figure 1) [32]. Patients with type 2 diabetes registered at PCNs will be invited to participate in an ongoing, annual survey as part of a larger Alberta’s Caring for Diabetes (ABCD) Cohort Study. Initial contact with cohort participants includes the administration of the Patient Health Questionnaire, a brief depression screening survey, and if positive for depressive symptoms, respondents will be invited to participate in the TeamCare-PCN study. We will allocate eligible participants to the intervention and usual care arms using an “on-off” time series (Figure 1); all participants will be assessed at baseline, 6 and 12 months.

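### Depression remission, a non-primary endpoint, requires PHQ-9 below 10 for three consecutive months, but the common schedule of baseline, 6 and 12 months cannot show that state in either arm

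*Protocol article*

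**What the plan says.** The definition appears twice. Under Depression-related outcome: "A remission of depression symptoms is indicated with a score <10 for a period of three consecutive months". Under Data analysis, the arms are to be compared on "the proportion of subjects who achieved a remission of depression (i.e., PHQ-9 < 10 for 3 consecutive months", and the results are to be given as absolute differences and a number-needed-to-treat. Remission also serves as the worked example for proportions under Sample size and power considerations (45% in usual care against 60% with the intervention).

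The schedule appears three times: in the abstract, under Overall study design ("all participants will be assessed at baseline, 6 and 12 months"), and under Outcome measures ("All outcomes will be measured in all participants (i.e., both groups) at baseline, 6, and 12 months").

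Three further statements bear on who could supply more frequent scores:

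- Patient management, intervention arm: "The CM will actively follow-up by telephone or in person one to two times per month to re-assess symptoms".
- Usual care: "patients will receive care from their family physician, without additional active support from the CM". The section adds: "Participants in this group will be assessed for all of the same outcome measurements as intervention patients".
- Data management: "The depression and medical outcome measures will be entered into a clinical management tracking system as part of the TeamCare-PCN intervention". Survey and clinical data go into centralized study databases, and at the end all data are exported and merged into one analysis dataset.

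**The concern.** The endpoint requires a state that lasts three months. The schedule provides single readings half a year apart. The article fixes both the definition and the schedule, so an analysis plan could reconcile them only by overriding one of them.

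What is at stake is one named between-arm comparison with its absolute difference and number-needed-to-treat. If the rule is left as it stands, someone must choose a substitute later, possibly with data in hand. One substitute within reach, care-manager readings, exists in one arm only and comes from the nurse who delivers the treatment.

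**Working it through.** **Step 1: definition against schedule.** The rule needs PHQ-9 values covering three consecutive months, about three monthly readings. After baseline the schedule gives readings at months 6 and 12, a gap of 12 - 6 = 6 months. Any three-month window therefore holds at most one reading. This applies equally to both arms, because the schedule is stated for both groups. Last-observation-carried-forward does not help: the intermediate readings were never scheduled, so they are not missing values to be filled.

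**Step 2: what remains computable.** The 12-month PHQ-9 score, the scaled marginal model for A1c, LDL cholesterol and systolic blood pressure, the 5-point PHQ-9 reduction and the 10% improvements all use scheduled visits. None of them needs the three-month rule.

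**Step 3: where extra readings could come from.** One to two care-manager contacts a month make about 12 to 24 in a year, in the intervention arm only. The article says that these contacts re-assess symptoms; it does not say that the PHQ-9 is given each time. It neither says that such readings feed the remission endpoint nor rules it out.

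**Step 4: the plan's own figure for remission.** The article claims more than 80% power for 45% against 60% with 60 per arm, two-sided 0.05. By the normal approximation, z = (0.15 x sqrt(60) - 1.96 x sqrt(2 x 0.525 x 0.475)) / sqrt(0.45 x 0.55 + 0.60 x 0.40) = (1.162 - 1.384) / 0.698 = -0.32, which is 37.5% power. The claim does not reproduce. That is a separate matter, and nothing here depends on it.

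**Step 5: size of the artefact if the arms used different rules.** This is an illustration with no treatment effect. Both arms follow the same course: mean PHQ-9 of 15 falling to 10.5 by month 6, SD 5, six-month correlation 0.6, patients with baseline of at least 10 retained. The 0.6 matches the repeated-measures correlation in the sample-size section; the means and SD are assumptions. The correlation between months is either constant or decays with the time between them.

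| Rule | Constant | Decaying |
|---|---|---|
| Any three consecutive months below 10 | 35.1% | 47.6% |
| Months 10 to 12 all below 10 | 16.6% | 30.6% |
| Month 12 alone below 10 | 39.1% | 41.9% |
| Months 6 and 12 both below 10 | 23.7% | 25.5% |

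Differences in percentage points, monthly rule in the intervention arm minus visit rule in usual care:

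- Any three months against month 12 alone: 35.1 - 39.1 = -4.0; 47.6 - 41.9 = +5.7.
- Any three months against months 6 and 12: 35.1 - 23.7 = +11.4; 47.6 - 25.5 = +22.1.
- Months 10 to 12 against month 12 alone: 16.6 - 39.1 = -22.5; 30.6 - 41.9 = -11.3.
- Months 10 to 12 against months 6 and 12: 16.6 - 23.7 = -7.1; 30.6 - 25.5 = +5.1.

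A cruder model (45% chance of a score below 10 in each month, month-to-month persistence 0 to 0.8) shows the same dependence on the rule: about 48-70% for any three months, 9-36% for months 10 to 12, 45% for month 12 alone, and 20-27% for months 6 and 12.

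**The case against.** The strongest reply is that this is a minor endpoint and that the article does nothing unequal. Much of that stands. Remission is not one of the two primary outcomes, and in the power statement it is only an example. All outcomes in both groups are on one schedule, usual care gets the same outcome measurements, and investigators and analysts are to be masked, which sits badly with drawing outcome data from one arm's tracking system.

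Three stronger readings are tempting, and the document does not support them:

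- *Usual-care remission would be 0%.* An unobserved state is undetermined, not absent. The same schedule would give 0% in the intervention arm too.
- *Care-manager readings will be used for the intervention arm.* No section says so. The risk is open only because those readings are not excluded from the merged data.
- *The comparison is biased towards the intervention by 11 to 22 points.* That range comes from one pairing of rules, and the both-visits rule does not appear in the article. Other pairings give small or negative differences.

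The reply does not remove the contradiction. Giving usual care the same measurements adds no time points, and no section reconciles the three-month rule with the visits.

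**Conclusion.** The point holds as an unworkable definition of a non-primary endpoint. On the stated schedule, remission cannot be determined in either arm, so the planned comparison of proportions, its absolute difference and its number-needed-to-treat cannot be produced as written. This follows from the text alone and rests on no simulation.

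Differential ascertainment is a possibility that the article leaves open, not a demonstrated bias. Under the assumed identical courses, the artefact from mixed rules runs from about -22 to +22 points across the pairings shown. The useful conclusion is that the rule must be settled before the data are seen, not that the result would lean one way. The primary analyses are not in question. The correction is worth making because the endpoint is wrong as written and cheap to repair.

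**What to change.** For the analysis endpoint only:

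- Define remission from the scheduled study assessments, identically in both arms: PHQ-9 below 10 at 12 months, with below 10 at both 6 and 12 months as the sustained version.
- State that PHQ-9 scores from care-manager contacts or the tracking system are not used as outcome data.
- Bring Depression-related outcome and Data analysis, which already agree with each other, into line with the schedule under Overall study design and Outcome measures.
- Make the remission example under Sample size and power considerations refer to the same definition.
- Leave the clinical use of the word remission under Patient management unchanged.

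The cost is a change of wording with no new data. The endpoint loses its three-month persistence element, which the schedule could not deliver. If persistence matters to the investigators, the alternative is identical monthly PHQ-9 collection by masked assessors in both arms, which does require new data and adds contact in usual care.
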